### Study design

This will be a prospective, randomized, controlled clinical effectiveness trial in pregnant women with malnutrition comparing the impact of combined nutrition and infection control interventions with the standard of care in Sierra Leone. The study will enroll pregnant women at less than 35 weeks of gestation with moderate or severe malnutrition. A probable patient diagram is shown in Fig. 1.

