### Eligibility criteria

Pregnant women presenting to any of the thirty selected antenatal clinics will be screened for enrolment eligibility. Women who have a fundal height no greater than 35 cm, MUAC ≤23 cm, and planning to reside in the study area and attend the antenatal clinic will be considered eligible. MUAC is a reproducible, reliable measure in the field and easily understandable by both health workers and participants. Fundal height will be used as a measure of gestational age. Exclusion criteria will include pregnant women less than 16 years of age who do not have an adult community member willing to consent for them or known complications of pregnancy such as gestational diabetes, pre-eclampsia, hypertension, or severe anemia.

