### Outcome measures

The primary outcome measure of interest will be birth length in centimeters. The secondary outcome measures of interests include the total and average weekly maternal weight gain, recovery from maternal malnutrition identified as a MUAC > 23, newborn head circumference, birth weight, infant linear and ponderal growth, and infant survival at 3 months and 6 months.

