### Subject participation and data collection

A study team member will attend each participating antenatal clinic for subject recruitment. All women attending the antenatal clinic will be briefly informed of the study and entry criteria in a group setting. Women willing to be measured and potentially participate will be offered measurement of MUAC and screened for study eligibility.

All women meeting eligibility criteria will be offered enrollment and agree via informed consent. Informed consent will be obtained by the on-site study coordinator. All participants who are 16 years of age or older will be able to consent for themselves as adults. If a participant who is younger than 16 wants to participate in the study, they will be required to have consent from a parent or guardian. Upon enrollment, the participant will be interviewed. Demographic information will be recorded, as well as, time of last menses, estimated date of delivery, and fundal height. Anthropometry will include current weight, height, MUAC, and weight history if available. Available medical records of the women will be reviewed with attention to any current or previous pregnancy complications and medications. Subjects will answer a standard clinical symptoms questionnaire, a food frequency questionnaire, and a Household Food Insecurity Access Scale (HFIAS).

Participants will return for follow-up every 2 weeks for measurements and provision of food until delivery. Since birth measurements are primary outcomes, a birth weight team will be identified and trained in order to obtain accurate birth measurements within 48 h of delivery.

Participation in the study will continue throughout pregnancy, and follow-up with the mother and infant will continue until 6 months postpartum. Mothers and infants will be followed at usual infant clinic follow-up at 6 weeks, 3 months, and 6 months post-partum contact point clinic. Infant weight, linear growth, and morbidity will be monitored. Maternal weight, MUAC and morbidity will be assessed at these visits, as well.

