### Interventions to reduce inflammation

The intervention group will receive a package of five interventions aimed at decreasing the burden of infections in pregnant women in order to decrease the risk of stillbirth, fetal growth restriction, and premature delivery. This package will include an insecticide-treated mosquito net at the time of enrollment, sufadoxine-pyrimethamine given every 4 weeks beginning at 13 weeks gestation, azithromycin given at the time of enrollment and at 28–34 weeks of gestation, single dose of albendazole at enrollment, and testing and treatment for bacterial vaginosis at enrollment and again in the third trimester. Table 4 details the anti-inflammatory interventions.

**Table 4 Tab4:** Anti-Inflammatory Interventions, Dosing, and Timing of Administration

Intervention	Dose	Time of administration
Insecticide-treated mosquito net	n/a	• Enrollment
Sulfadoxine-pyrimethamine	1500 mg/ 75 mg	• Enrollment or 13 weeks gestation, whichever is later • Every 4 weeks until delivery
Azithromycin	1 g	• Enrollment or second trimester, whichever is later • Weeks 28–34
Albendazole	400 mg once	• Enrollment or second trimester, whichever is later
Testing and treatment for bacterial vaginosis with metronidazole	750 mg PO daily for 7 days	• Enrollment • Weeks 28–34

The control group will receive the current recommendations of the government of Sierra Leone, which includes 60 mg iron and 400 μg folic acid supplementation starting at enrollment, an insecticide-treated mosquito net at the time of enrollment, three doses of sulfadoxine-pyrimethamine during second and third trimester, and a single dose of albendazole for deworming at enrollment.

Table 5 provides a summary of the schedule of activities and interventions for subjects by week of study participation.

**Table 5 Tab5:** Schedule of activities/ interventions for subjects by week of study participation

	Study Period									
	Enrollment									
Week	0	2	4	6	8	Third trimester	Delivery	6 weeks post-partum	3 months post-partum	6 months post-partum
Enrollment:										
Eligibility Screen	X									
Informed consent	X									
Socio-demographic questions	X									
Assessments:	X				X					
HFIAS^a^, Food frequency questionnaire	X				X					
Clinic visit for intervention and control food supply	X	X	X	X	X					
Adherence/educational messages	X	X	X	X	X					
Surveillance of clinical events	X	X	X	X	X					
Maternal anthropometric measurements	X	X	X	X	X					

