### Statistical analysis

Descriptive statistics will be used to characterize the population. Student’s t-test will be used to assess whether primary outcomes of infant birth weight and length, and secondary outcome of maternal weight gain improved significantly in the intervention group compared with the control. Fisher’s exact test will be used to determine if the proportion of mothers recovering from malnutrition and of infants with LBW are improved in the intervention group. Regression modeling will be used to investigate factors that influence maternal and infant outcomes. Independent variables to be considered as covariates for inclusion in the models include: maternal age, weight, number of previous pregnancies, anemia, illness and number of weeks of intervention. For longitudinal measures, the groups will be compared using repeated measures mixed model analysis of variance. Covariates will include age, number of previous pregnancies, years of education and clinic location.

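### Maternal weight gain is compared by an unadjusted t-test although women are observed for about 2 to over 25 weeks; the test is valid, but it is imprecise and leaves a difference in total gain hard to interpret

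*Protocol article*

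**What the plan says.** Under Outcome measures, the secondary outcomes include "the total and average weekly maternal weight gain". The Statistical analysis section assigns Student's t-test to this outcome by name: it asks whether the "secondary outcome of maternal weight gain improved significantly in the intervention group compared with the control". No covariates or weights are attached to that test.

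The same section has two other strands. Regression models will explore influences on outcomes, with the number of weeks of intervention among the candidate covariates. And: "For longitudinal measures, the groups will be compared using repeated measures mixed model analysis of variance", with age, parity, education and clinic as covariates. The section does not say that maternal weight is one of those longitudinal measures.

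On timing, Study design says "The study will enroll pregnant women at less than 35 weeks of gestation", and Eligibility criteria say "Women who have a fundal height no greater than 35 cm". Neither sets a lower limit. Table 4 foresees entry before 13 weeks, since one intervention starts at "Enrollment or 13 weeks gestation, whichever is later". Under Subject participation and data collection: "Participants will return for follow-up every 2 weeks for measurements and provision of food until delivery". Weight and fundal height are recorded at enrolment. The section on interventions to reduce inflammation gives fewer premature deliveries as one aim of the package.

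**The concern.** The length of observation differs greatly between women, and the named test ignores it.

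- **Total gain** grows with the weeks observed. Variation in entry time enters the error term of the t-test, although most of it could be removed with a measure taken at enrolment. The end of the interval is delivery, which comes after randomization and which the package is meant to influence. A difference in total gain may therefore reflect faster gain, longer pregnancy or both.
- **Average weekly gain** is already divided by time, so it has no such tie to duration. Its problem is unequal precision: a rate from one fortnightly interval counts as much as a rate from a dozen.

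At stake are the precision and reading of one secondary outcome. The primary outcome is not touched.

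**Working it through.** **1. The plan's own figure.** There is none to reproduce. The Sample size section covers birth length and birth weight and gives no SD, target difference or power for maternal weight gain. All weight-gain inputs below are therefore assumptions, shown as ranges.

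**2. Length of observation T (inferred).** Latest entry is about 35 weeks: 40 - 35 = 5 weeks to a 40-week delivery and 37 - 35 = 2 weeks to a 37-week delivery. Entry at 13 weeks gives 40 - 13 = 27 weeks.

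**3. Variance of total gain.** With mean rate m, between-woman SD of rate sb and within-woman weight SD se:

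Var(total) = m²·Var(T) + sb²·E[T²] + 2·se²

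Example: T uniform on 2-27 weeks, m = 0.30 kg/week, sb = 0.15 kg/week, se = 0.5 kg.
- Var(T) = 25²/12 = 52.1; E[T²] = 52.1 + 14.5² = 262.3
- Terms: 0.09 × 52.1 = 4.69; 0.0225 × 262.3 = 5.90; 2 × 0.25 = 0.50; sum 11.09
- Share due to T: 4.69/11.09 = 42%
- Detectable difference with 600 per arm (80% power, two-sided 0.05): 2.80 × √(2 × 11.09/600) = 0.54 kg. With the T term removed completely it is 2.80 × √(2 × 6.40/600) = 0.41 kg.

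The 0.41 kg is a limit, not a target, because part of T is fixed only at delivery.

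**4. Range.** By simulation: entry uniform from 13 or 20 to 35 weeks, delivery at 38.8 weeks (SD 2), follow-up cut to whole fortnights, sb 0.10-0.20, se 0.5-1.2. Observation length gives an SD of 1.4-2.0 kg in total gain, about 20-58% of its variance.

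**5. How much of T is known at enrolment.** Entry at 13-35 weeks has variance 22²/12 = 40.3 and delivery 2² = 4, so 40.3/44.3 = 91%. Entry at 20-35 weeks gives 18.75/22.75 = 82%. If fundal height measures gestation with an assumed error of 2 weeks, it explains about 13-47% of the variance of total gain. The standard error would then fall to √0.87 = 0.93 or √0.53 = 0.73 of its unadjusted size.

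**6. Mixing of rate and duration.** Shift in total gain = difference in gestation × weekly rate, with no change in rate: 0.2 week × 0.2 kg = 0.04 kg up to 1.0 week × 0.4 kg = 0.40 kg.

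**7. Average weekly gain.** The variance of a first-to-last rate is sb² + 2·se²/T². With sb 0.15 and se 0.5 it is 0.0225 + 0.5/4 = 0.148 at T = 2 and 0.0225 + 0.5/676 = 0.023 at T = 26. Efficiency of the equal-weight mean against inverse-variance weighting:

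| T | sb 0.15, se 0.5 | range (sb 0.10-0.20, se 0.3-1.0) |
|---|---|---|
| uniform 2-27 weeks | 0.87 (600 per arm acts like 521; 80% power becomes 74%) | 0.45-0.98 |
| uniform 5-27 weeks | 0.98 (79% power) | 0.78-1.00 |

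Against a slope model on all fortnightly weights under the step 4 inputs, the variance ratio is about 1.1 to 3.2. It is 1.55 with sb 0.15, se 0.8 and entry from 13 weeks. In that case the 10% of women with 4 weeks or less supply 38% of the variance, and leaving out the roughly 3% with a single 2-week interval lowers the ratio to 1.27.

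**8. Validity.** With T distributed alike in both arms (uniform 2-27 weeks, 600 per arm, 4000 runs), the simulated type I error of the t-test on weekly gain is 5.2%.

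**The case against.** The strongest reply has four parts.

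- **The t-test is valid.** Randomization balances gestation at entry, and the simulated error rate agrees. This stands. A reader might infer that the comparison is biased by unequal follow-up; the documents do not support that.
- **The remedy is already planned.** Fortnightly weights are an obvious longitudinal measure, and weeks of intervention is a listed covariate. This stands only in part. The section sends weight gain to the t-test by name and does not link the mixed model to it. Weeks of intervention is a candidate in an exploratory regression, and it is a post-randomization quantity that the package may change.
- **Two outcomes are named, and weekly gain is scaled to time.** A reader can compare the two, and in an effectiveness trial gain from a longer pregnancy is arguably part of the benefit. This stands. It calls for stating how total gain is to be read, not for discarding it.
- **The sizes are fragile.** No input comes from the document, and the weekly-gain loss rests largely on a few women with very short follow-up. This stands for weekly gain. A slope model also favours women observed longer and assumes near-constant gain, so making it the sole analysis would change what is estimated.

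**Conclusion.** The point holds as one of precision and interpretation for a secondary outcome. The unadjusted t-test is valid but leaves avoidable noise in total gain: about 20-58% of its variance comes from observation length, and 82-91% of the variance in that length is set at entry under the assumed entry windows. A between-arm difference in total gain combines rate and duration, by about 0.04-0.40 kg for an assumed 0.2-1.0 week difference in gestation. For average weekly gain only precision is at issue, and the loss ranges from negligible to more than half of the information, depending on how many women have very short follow-up and how noisy the weights are.

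Two stronger readings should be resisted. Total gain does not depend mainly on observation length; in most of the assumed settings the share is below half. And the 1.4-2.0 kg SD is noise shared by both arms, not evidence of a between-arm shift. All sizes rest on assumed rates, SDs and entry distributions.

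**What to change.** In the Statistical analysis section, replace the t-test for maternal weight gain with a linear model by arm, adjusted for enrolment fundal height, enrolment weight and clinic, for both total and average weekly gain. State that this group comparison is not adjusted for realised weeks of intervention. Name the mixed model already in that section, applied to all fortnightly maternal weights with arm-by-time as the effect, as the supporting analysis of rate of gain. Add that a difference in total gain will be read as a combined effect of rate and pregnancy duration.

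The cost is wording and slightly more analysis work; the data are already collected. The trade-off is that the mixed model gives more weight to women observed longer and assumes near-linear gain, which is why it supports the adjusted comparison and does not replace it.

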**Methods/design:**

This will be a prospective, randomized, controlled clinical effectiveness trial of an improved supplementary food plus anti-infective therapies compared to standard therapy in malnourished pregnant women. Pregnant women will be randomized to receive a low water activity, ready-to-use supplementary food plus five anti-infective interventions or the standard of care which is 3.5 kg corn/ soy blended flour with 350 mL vegetable oil every two weeks. The five anti-infective interventions are 1) insecticide-treated mosquito net at the time of enrollment into the study, 2) sulfadoxine-pyrimethamine given every 4 weeks, beginning at enrollment or at 13 weeks’ gestation, whichever is later, 3)azithromycin at a dose of 1 g given once at enrollment (after first trimester)and again during 28–34 weeks of gestation, 4)single dose 400 mg albendazole given in second trimester, and 5) testing and treatment for bacterial vaginosis at enrollment and again at 28–34 weeks of gestation. Treatment will be provided for the duration of the pregnancy. The primary outcome measure will be birth length. Secondary outcomes in the mothers will include rates of maternal weight gain and increase in mid-upper arm circumference, and time to maternal anthropometric recovery. Secondary outcomes in the infants will include birth weight, birth head circumference, and linear and ponderal growth.

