#### Control group food

The control group will receive the standard of care for malnourished pregnant women in Sierra Leone which is 3.5 kg super cereal with 350 mL vegetable oil every two weeks. This provides 250 mg portion per day of the super cereal and 25 g oil per day for the mother. Iron and folic acid supplement goal is 90 pills through pregnancy.

The study will assure that women have an uninterrupted access to the ready to use local supplementary food and super cereal if they are in the control group. Table 3 provides a comparison of the nutritional composition of the study RUSF, standard of care food, and recommended daily intake for pregnancy. Women will receive the food for the duration of their pregnancy.

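### Weeks of intervention, a candidate covariate in the exploratory regression models, contains length of gestation, so its slope on birth size cannot be read as a dose-response

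*Protocol article*

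**What the plan says.** The Statistical analysis section gives the regression models an explanatory purpose: "Regression modeling will be used to investigate factors that influence maternal and infant outcomes". It then offers a candidate list, introduced by "Independent variables to be considered as covariates for inclusion in the models include", which names maternal age and weight and ends with "number of previous pregnancies, anemia, illness and number of weeks of intervention". No time of measurement is attached to any item, and treatment arm is not named in the list.

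The arm comparisons are set out separately. Student's t-test "will be used to assess whether primary outcomes of infant birth weight and length" and maternal weight gain improve. Fisher's exact test covers maternal recovery and low birth weight. A repeated-measures mixed model covers longitudinal outcomes, with its own covariates (age, parity, schooling and clinic).

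On duration, the abstract says "Treatment will be provided for the duration of the pregnancy", and the Control group food section says "Women will receive the food for the duration of their pregnancy". Table 4 continues sulfadoxine-pyrimethamine until delivery. On entry, the Study design section says "The study will enroll pregnant women at less than 35 weeks of gestation with moderate or severe malnutrition". On purpose, the section on interventions to reduce inflammation says the package is given "in order to decrease the risk of stillbirth, fetal growth restriction, and premature delivery".

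**The concern.** Weeks of intervention cannot be a baseline variable. The clock starts at enrolment and stops at delivery, so the count is settled by the birth itself. A later birth gives more weeks and a longer, heavier baby, whatever was in the sachet. This holds in both arms, because both receive food until delivery.

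Two consequences follow if the variable is entered in a model of birth length or weight. First, its slope mixes any benefit of longer exposure with ordinary fetal growth. A finding that more weeks go with longer babies would invite a message about early enrolment, and the Discussion presents the bundle as a possible model for national programmes. Second, if arm is in the same model, adjusting for weeks conditions on something the package is meant to change, since fewer premature deliveries means longer gestation.

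**Working it through.** The plan gives no figure for this point. It supplies the evaluable sample (1200) and the SD implied by the Sample size section: 0.5 cm / 0.22 = 2.27 cm. The remaining inputs are assumptions.

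**Assumptions**
- Birth length rises b = 0.6 cm per week of gestation.
- Gestational age at birth has SD 2 weeks (variance 4) and is independent of gestational age at enrolment.
- Enrolment is uniform over 14 to 35 weeks (variance 21²/12 = 36.75) or over 20 to 30 weeks (variance 10²/12 = 8.33).

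**Step 1. Identity.** weeks = GA at birth − GA at enrolment, so Var(weeks) = 4 + 36.75 = 40.75, or 4 + 8.33 = 12.33.

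**Step 2. Slope on weeks for an inert product.** slope = b × Var(GA at birth) / Var(weeks).
- 14 to 35 weeks: 0.6 × 4 / 40.75 = 0.059 cm per week
- 20 to 30 weeks: 0.6 × 4 / 12.33 = 0.195 cm per week

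At these slopes the design difference of 0.5 cm is matched by 0.5 / 0.059 = 8.5 extra weeks, or 0.5 / 0.195 = 2.6 extra weeks, with no product effect at all.

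**Step 3. Would it be significant with 1200 women?** SE = residual SD / (√1200 × SD of weeks).
- 14 to 35: residual SD = √(2.27² − 0.059² × 40.75) = 2.24; SE = 2.24 / (34.64 × 6.38) = 0.0101; t = 5.8
- 20 to 30: residual SD = √(2.27² − 0.195² × 12.33) = 2.16; SE = 2.16 / (34.64 × 3.51) = 0.0178; t = 10.9

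A simulation of 400 trials gave the same mean t values, with every run significant.

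**Step 4. Effect on an arm coefficient, if arm is in the model.** Suppose a direct effect of 0.25 cm and gestation prolonged by 0.4 week, so the total is 0.25 + 0.6 × 0.4 = 0.49 cm. Adjusting for weeks removes slope × 0.4.
- 14 to 35: 0.059 × 0.4 = 0.024; 0.024 / 0.49 = 5%; 0.47 cm left
- 20 to 30: 0.195 × 0.4 = 0.078; 0.078 / 0.49 = 16%; 0.41 cm left
- No prolongation: slope × 0 = 0, so nothing is removed

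**Step 5. Sensitivity.** With b from 0.6 to 0.9 cm per week, enrolment over 13 to 35, 20 to 35 or 20 to 28 weeks, and a total effect of 0.5 cm, large-sample simulation gave slopes on weeks of 0.05 to 0.39 cm per week. With gestation prolonged by 0.2 to 0.5 week, weeks alone removed about 2 to 38% of the arm effect.

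**The case against.** The strongest reply is that no stated arm comparison uses these models. The primary test is unadjusted, the proportions go to Fisher's exact test, and the mixed model has other covariates. The list is one of candidates, for models that explore influences on outcome. This stands, and it confines the point to a secondary analysis. A reader might infer that the efficacy result itself is at risk. The document does not support that: the regression would have to replace the stated tests, and nothing says it will.

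A reader might also infer that half the effect would be lost. With gestational age at enrolment added alongside weeks, the slope on weeks becomes the full 0.6, and 0.6 × 0.4 = 0.24 of the 0.49 cm is removed. The candidate list contains neither enrolment gestation nor fundal height, so this is not the model described.

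A third tempting reading is that illness and anemia are post-randomisation mediators. The package does aim to reduce infection, and Table 5 schedules surveillance of clinical events up to week 8. But the article does not say which measurement would be used, and that detail may sit in the analysis plan. A symptom questionnaire and a record review take place at enrolment, and Table 5 shows no later anemia test. Enrolment values would be harmless.

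Finally, the models cover maternal outcomes too. For total maternal weight gain, time under observation is an ordinary explanatory variable. This also stands, and limits the point to birth outcomes.

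**Conclusion.** The point holds for weeks of intervention in regression models of birth length and birth weight. That the variable contains gestation length follows from the protocol's own treatment period and needs no assumption. The size does: about 0.06 to 0.19 cm per week of apparent benefit from an inert product under the main inputs, and 0.05 to 0.39 over the wider set. Any loss of arm effect is conditional on arm being estimated in that model and on the package prolonging gestation. It is then roughly 5 to 16% for an assumed 0.4 week.

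This is worth correcting because the false slope would very likely reach significance in 1200 women and could be taken as evidence about when to start treatment. It does not threaten the primary comparison.

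**What to change.** In the regression models for birth outcomes, replace weeks of intervention with gestational age at enrolment, from last menses or fundal height. Substitute it; do not add it beside weeks, since having both in the model removes more of any arm effect. To ask whether longer exposure helps, fit an arm-by-enrolment-gestation interaction: enrolment gestation is fixed before randomisation, and for an inert product the interaction is zero in expectation.

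In any model that estimates the arm effect, use illness and anemia only as recorded at enrolment. Label any model containing post-randomisation variables as exploratory and not an estimate of the treatment effect.

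The cost is a sentence or two. Last menses, expected delivery date and fundal height are already collected at enrolment (Subject participation and data collection). That section lists no hemoglobin measurement, so enrolment anemia would have to come from whatever the record review yields, or be left out.

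### The covariates listed for the longitudinal mixed model omit the enrolment value of the outcome and gestation at enrolment, so any comparison of serial maternal MUAC or weight is less precise than the collected data allow

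*Protocol article*

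**What the plan says.** The Statistical analysis section of the protocol article assigns methods as follows.

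- Student's t-test: birth weight, birth length and the "secondary outcome of maternal weight gain improved significantly in the intervention group compared with the control".
- Fisher's exact test: low birth weight and maternal recovery ("Fisher’s exact test will be used to determine if the proportion of mothers recovering from malnutrition").
- Exploratory regression models, with candidate covariates "maternal age, weight, number of previous pregnancies, anemia, illness and number of weeks of intervention".
- Mixed model: "For longitudinal measures, the groups will be compared using repeated measures mixed model analysis of variance". The next sentence gives its covariates: "Covariates will include age, number of previous pregnancies, years of education and clinic location".

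The section does not name the longitudinal measures, the visits that serve as responses, or the term tested.

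The abstract's Methods/design paragraph lists maternal outcomes: "Secondary outcomes in the mothers will include rates of maternal weight gain and increase in mid-upper arm circumference, and time to maternal anthropometric recovery". Under Subject participation and data collection, fundal height, last menses and estimated delivery date are recorded at enrolment, and "Anthropometry will include current weight, height, MUAC, and weight history if available". Follow-up is fortnightly until delivery. Table 5 marks maternal anthropometry at weeks 0, 2, 4, 6 and 8.

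**The concern.** Increase in MUAC is a secondary outcome in the abstract and has neither a t-test nor a Fisher test. Of the group comparisons stated, the mixed model is the one that fits it, and the model also fits the serial maternal weights. For both, a woman's own starting value is likely to explain much of the later variation. For weight, how far the pregnancy had advanced at entry should matter too, because women enter at any fundal height up to 35 cm. The stated list leaves out both and keeps age, previous pregnancies, education and clinic. The exploratory regression list does have maternal weight, so the difference lies between two lists in the same section.

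What is at stake is efficiency on secondary maternal outcomes: a real effect on maternal nutritional status could be missed, or estimated with a wider interval than necessary.

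**Working it through.** No figure in the article rests on the mixed model. The sample size (600 per group after losses, two-sided 0.05, 80% power) is set for birth length and birth weight. There is therefore nothing to reproduce here, and the inputs below are partly assumed.

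**Inputs.** From Table 5: m = 4 follow-up visits after enrolment. From Sample size: two-sided 0.05. Assumed, because the article gives no value: the same correlation rho between any two visits (0.5 to 0.9), the same variance (1) at each visit, complete data, and a constant effect over follow-up. The 80% power used as a starting point is hypothetical; the changes from it do not depend on the number of women.

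**Variance per woman of each contrast**

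- Follow-up mean, enrolment value unused: V1 = (1 + (m − 1)rho)/m
- Follow-up mean minus enrolment (group-by-time with enrolment as a response): V2 = V1 + 1 − 2rho
- Follow-up mean adjusted for enrolment: V3 = V1 − rho²

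At rho = 0.5: V1 = 2.5/4 = 0.625; V2 = 0.625 + 1 − 1 = 0.625; V3 = 0.625 − 0.25 = 0.375.

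| rho | V1 | V2 | V3 | Cut against V1 | Cut against V2 |
|---|---|---|---|---|---|
| 0.5 | 0.625 | 0.625 | 0.375 | 40% | 40% |
| 0.7 | 0.775 | 0.375 | 0.285 | 63% | 24% |
| 0.8 | 0.850 | 0.250 | 0.210 | 75% | 16% |
| 0.9 | 0.925 | 0.125 | 0.115 | 88% | 8% |

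**Power.** An effect with 80% power sits at 1.960 + 0.842 = 2.802 standard errors. After adjustment this becomes 2.802/√(V3/V1) or 2.802/√(V3/V2). At rho = 0.5 it is 2.802/√0.60 = 3.617, and 3.617 − 1.960 = 1.657 gives 95%. Against V1 at rho = 0.7, power exceeds 99%. Against V2 at rho = 0.7, 0.8 and 0.9, it is 90%, 86% and 83%.

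**Main effect averaged over all visits, enrolment included.** A constant effect is multiplied by m/(m + 1) = 0.80, with variance (1 + m·rho)/(m + 1). At rho = 0.5 this gives 2.802 × 0.80 × √(0.625/0.600) = 2.288, or about 63% power in place of 80%; at rho = 0.7 it gives 62%. With m = 8 the multiplier is 8/9 = 0.89 and power is about 70%. For a group-by-time test the multiplier does not apply.

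**Entry cut-off for MUAC.** Eligibility requires MUAC of 23 cm or less, which shrinks the enrolment variance to some fraction u and breaks the equal-variance assumption for MUAC. Selection on the enrolment value leaves the regression slope unchanged, so V3 stays the same, V1 becomes V3 + rho²u and V2 becomes V3 + (1 − rho)²u. Suppose the population rho is 0.8 and the lowest 20% enrol (both assumed; for a normal distribution u = 0.22). Then V3 = 0.210, V1 = 0.210 + 0.64 × 0.22 = 0.351 and V2 = 0.210 + 0.04 × 0.22 = 0.219. The cuts are 40% against V1 and 4% against V2. For MUAC, the gain over a change contrast may therefore lie below the table's range.

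**Gestation.** The article gives no correlation between gestation and either measure, so this part of the gain cannot be sized.

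**The case against.** The strongest reply is that the article does not tie the mixed model to maternal measures. Maternal weight gain and recovery have their own tests. Increase in MUAC appears in the abstract but not under Outcome measures. Infant linear and ponderal growth fits the phrase at least as well and has no pre-randomisation value to adjust for. This stands: the link to MUAC is by elimination, and the point applies only where the model is used for maternal measures.

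Second, "Secondary outcomes in the mothers will include rates of maternal weight gain and increase in mid-upper arm circumference" describes change, so group-by-time is the natural test, and Table 5 puts enrolment among the measurement visits. That model already uses the enrolment value. This also stands, and it moves the gain to the last column of the table, or lower for MUAC. It does not remove the gain.

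Third, the list need not be closed, and response visits and the tested term are details an article may leave to a full plan. Their absence is not criticised here. The covariates, however, are stated, and they leave out an obvious one already collected.

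A reader might go further and infer that including enrolment as a response dilutes the effect towards no difference. The article does not support that. Dilution also requires testing a main effect averaged over enrolment and follow-up, which the article nowhere says will be done.

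**Conclusion.** The point holds as a matter of efficiency. For maternal longitudinal measures, adding the enrolment value improves precision whether it would otherwise be unused or used through a change contrast. The gain is large in the first case and moderate to small in the second. The sizes rest on compound symmetry, four complete follow-up visits and an assumed rho; unequal visit numbers, which fortnightly follow-up to delivery will produce, would alter them. Randomisation keeps both the follow-up comparison and the group-by-time comparison unbiased, so this is not a claim of bias. Only secondary maternal outcomes are touched. Birth length, birth weight, the t-test on maternal weight gain, Fisher's test on recovery and infant growth are unaffected.

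**What to change.** In Statistical analysis, after the covariate sentence, add that for maternal longitudinal measures the responses are the post-enrolment visits, that the enrolment value of the same measure (MUAC or weight) and enrolment fundal height join the listed covariates, and that the group effect over follow-up is the term tested. An equivalent is to keep enrolment as a response with the two group means constrained equal at that visit, retaining fundal height as a covariate. Keep age, previous pregnancies, education and clinic as listed.

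The cost is one sentence and two more model terms. No new data, visits or participants are needed.
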